## Abstract

**Background:**

Cardiovascular diseases (CVDs) remain the leading causes of morbidity and mortality in the world. Hypertension is an important and prevalent cardiovascular risk factor. The present study will be conducted to investigate the effect of barberry as a cardio-protective fruit on the blood pressure in patients with hypertension and other CVD risk factors. Furthermore, plasma concentrations of lipids and inflammatory biomarkers will be evaluated.

**Methods/design:**

This is an 8-week, prospective, single-blinded, parallel assigned, randomized controlled clinical trial (RCT) in which eligible men and women with hypertension and other cardiovascular risk factors will be randomized to either placebo powder (PP; containing 9 g maltodextrin, 1 g citric acid, 1 g milled sucrose and edible red color (*n* = 37)) or barberry powder (BP; containing 10 g milled dried barberry and 1 g of milled sucrose (*n* = 37)) groups. At baseline and after 8 weeks of intervention, plasma lipids and inflammatory markers, 24-h urinary nitrite/nitrate and sodium excretion, and 24-h ambulatory blood pressure monitoring (ABPM) will be measured. Anthropometric measures and dietary assessment will be performed as well. Data analysis will be done using SPSS version-21 software.

**Discussion:**

The interest in natural and functional food products has increased globally. This RCT will add to the growing literature for the potential antihypertensive, lipid-lowering, and anti-inflammatory effects of barberry in humans.

**Trial registration:**

ClinicalTrials.gov (NCT number) NCT04084847. Registered on 10 December 2019.

## Introduction

Cardiovascular diseases (CVDs) remain the leading causes of morbidity and mortality in the world, as they account for about 30% of mortality worldwide [1]. These diseases are also one of the major priorities of the Iranian healthcare system [2], and it is estimated that the burden of the disease will increase more than twice as the elderly population increases until the 2025 years [3]. Hypertension is an important and prevalent cardiovascular risk factor that imposes a great burden on the healthcare system [4]. According to the World Health Organization (WHO) reports, hypertension affects half of the adults worldwide and its prevalence is dramatically increasing in all age groups [5]. The production of nitric oxide (NO) from arginine in vascular endothelial cells is important in vasodilation, maintaining vascular tone maintenance, and regulation of blood pressure (BP). Most of the NO produced is metabolized to nitrite and nitrate (NOx) and excreted in the urine [6].

A significant number of patients with hypertension have several cardiovascular risk factors. Diabetes and dyslipidemia are among the most important risk factors known for CVDs [7] which may coexist with hypertension. Besides, inflammatory mediators are involved in many cardio-metabolic disorders. Several inflammatory biomarkers have been investigated to improve cardiovascular risk prediction and to monitor the disease process. Among the pro-inflammatory biomarkers, C-reactive protein (CRP) and interleukin-6 (IL-6) are associated with an increased risk of cardiovascular events and progression [8].

Epidemiologic studies have shown that a high intake of fruits and vegetables reduces the risk of developing cardiovascular disease [9]. This may be due to bioactive compounds found in fruits and vegetables such as polyphenols. Findings from experimental and epidemiological studies suggest that dietary intake of polyphenol-rich foods could be effective in reducing cardiovascular events. Higher intakes of fruit-based flavonoids have been associated with a lower risk of nonfatal myocardial infarction and ischemic stroke [10, 11]. The Berry family is rich in polyphenols such as procyanidins, quercetin, phenolic acids, and especially anthocyanins [12]. The anthocyanins are effective antioxidants in preventing CVD due to inhibiting inflammatory processes, reducing endothelial dysfunction and causing vasodilation [13]. Studies have shown that consumption of berry fruits such as Elderberry, Cranberry, Bilberry, Blueberry, Whortleberry, and Black Raspberry can have beneficial effects on CVDs [14]. Regarding hypertension, beneficial effects of berry fruits on blood pressure in healthy as well as hypertensive individuals have also been reported [15–18].

*Berberis vulgaris* commonly known as barberry is cultivated in Europe and West Asia, among other countries, and its fruit is used in several different forms for culinary purposes, jams, and soft drinks. Owing to its berberine and anthocyanins content, the effects of this plant have been investigated concerning cardiovascular risk factors in experimental studies [19, 20]. There has been, however, limited clinical trial related to the effect of barberry on cardio-metabolic parameters. Lazavi et al. showed that 200 ml of barberry juice significantly improved systolic and diastolic blood pressure, fasting blood sugar, and blood lipids in people with type 2 diabetes [21]. Shidfar et al. showed that a daily intake of 3 g of barberry extract for 3 months had beneficial effects on blood lipids and lipoproteins, glucose, and total antioxidant capacity in diabetic patients [22]. Recently, a meta-analysis showed that barberry consumption is a safe approach for the management of lipid parameters [23]. Nevertheless, the previous studies regarding the effects of barberry on cardiovascular risk factors, especially hypertension, had various limitations. These include the lack of precise monitoring of blood pressure by an accurate none-invasive method such as 24-h ambulatory blood pressure monitoring (ABPM) and also not measuring 24-h urine sodium excretion as an estimate of sodium intake for its confounding influence in evaluating the intervention’s effects on blood pressure. Furthermore, the mechanism by which barberry may modulate blood pressure has not been well studied, including its potential effect on nitric oxide production, which can be assessed by measuring the 24-h urine NOx level. Considering the high prevalence of CVD and hypertension as well as the limited number of clinical trials on the effect of barberry on hypertension and other cardiovascular risk factor, further clinical trials are required in this area. Therefore, the present randomized clinical trial will be conducted to investigate the effect of supplementation with barberry fruit on the blood pressure by 24-h ABPM and on 24-h urinary NOx and sodium excretion in patients with hypertension and other CVD risk factors. Furthermore, plasma concentrations of lipids, lipoproteins and inflammatory biomarkers will be evaluated as the secondary outcomes.

### Main aim

This study aims to investigate the effect of barberry consumption on systolic blood pressure (SBP), diastolic blood pressure (DBP), mean arterial blood pressure (MAP), plasma lipids, and inflammation status in patients with hypertension and other cardiovascular risk factors.

### Primary objective

To evaluate the effect of 8-week barberry consumption on variations in SBP measures in patients with hypertension and other cardiovascular risk factors.

### Secondary objectives

To compare within- and between-group variations in DBP, MAP, plasma lipid profile including total cholesterol (TC), low-density lipoprotein cholesterol (LDL-C), high-density lipoprotein cholesterol (HDL-C), triglyceride (TG), inflammatory biomarkers including plasma CRP and interleukin-6, and 24-h urinary NOx in patients with hypertension and other cardiovascular risk factors.

### Hypotheses

Daily consumption of barberry will improve SBP, DBP, and MAP in patients with hypertension and other cardiovascular risk factors.

Plasma levels of lipids, CRP, and IL-6 will be reduced by daily consumption of barberry in patients with hypertension and other cardiovascular risk factors.

Urinary NOx will be increased by daily consumption of barberry in patients with hypertension and other cardiovascular risk factors.

## Methods/design

### Design

This is an 8-week, prospective, single-blinded, parallel assigned, randomized controlled clinical trial (RCT) in which men and women with hypertension and other cardiovascular risk factors will be randomized to an interventional (barberry) or placebo group (Fig. 1).

**Fig. 1 Fig1:**
[figure not shown]
CONSORT flow diagram

### Ethics, consent, and permissions

National Nutrition and Food Technology Research Institute (NNFTRI), Shahid Beheshti University of Medical Sciences, will provide financial support for the current project. The trial will be conducted in compliance with the Declaration of Helsinki. The trial has received ethical approval from the Ethics Committee of NNFTRI (2018-10-20: Ethical code: IR.SBMU.nnftri.Rec.1397.248).

### Participant recruitment

In this clinical trial, we will recruit a total of 80 participants both men and women (each group 40) with hypertension and other cardiovascular risk factors (diabetes and/or hyperlipidemia and/or smoking) in Tehran, the capital of Iran. Volunteers among patients with a previous history of hypertension who have a medical record in the academic hospital (Rajaei Cardiovascular, Medical & Research Center, Tehran, Iran) and are regularly visited in the hospital clinics every 4–6 months if they meet the eligibility criteria will be recruited. Besides, by placing an advertisement in the hospital, other volunteer people who are referred to the hospital if they meet the eligibility criteria are also included in the study. To guarantee achieving adequate participant enrolment, the clinic staff at the hospital will be informed about the study, and informational conversation with patients will be held.

The trial is due to last 9 months. This assumes 5 months for participant recruitment and intervention, 2 months for laboratory testing, 1 month for data preparation and analysis by SPSS software, and 1 month to write the study report. The study protocol has been reported in accordance with the Standard Protocol Items: Recommendations for Clinical Interventional Trials (SPIRIT) guidelines [24] (Additional file 1, SPIRIT Checklist). The trial schedule is shown in Table 1. Informed consent will be obtained from all subjects before collecting any information. After reviewing the consent forms and answering any probable questions by study staff, those who are interested will be asked to sign the forms. A copy of the consent form will be given to participants and all original signed consent forms will be kept by the study staff (Additional file 2, consent form).

**Table 1 Tab1:**
[figure not shown]
Time table of protocol

### Eligibility

The inclusion criteria for subjects include (1) willingness to participate in the study, (2) age between 20 and 65 years, (3) known hypertensive patients on medical treatment, and (4) at least one other classical CVD risk factors, including hyperlipidemia, diabetes mellitus, or smoking. Exclusion criteria include (1) unwillingness to continue participation, (2) having BMI > 30, (3) patients on nitrate drugs, (4) taking high doses of statins (Atorvastatin> 40 mg/day or Rosuvastatin> 20 mg/day), (5) consumption of vitamins or minerals supplements during the past month, and (6) having chronic kidney disease stage 4 or 5. The drop out criteria include any side effects, refusing to continue the study, missing telephone responses, and any restrictive illness. Participants are allowed to withdraw from the study at any time.

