### Setting

For those who are interested in participating in the trial, cardiologist and study staff will confirm if they have eligibility criteria, and the appointment will be set for their first visit. In the first visit, the potential participants will have the proposals of the research project fully explained to them, and all participants will be asked to fill in the consent form. A general information questionnaire, including demographic information, disease history, the type and dosage of their medications, occupation, education and the smoking status, physical activity questionnaire, and three food recall questionnaire will be completed from each participant. The next visit will be after 2 weeks run-in period of weight maintenance, when baseline data including body weight and fasting blood sample will be obtained and the patient will be instructed to collect urine within the next 24 h and an ABPM device will be installed. After 24 h, the collected urine sample will be delivered and the results of the ABPM device will be stored. The patient will be given barberry or placebo packages and instruction on how to record their consumption. The next meeting will be at the end of the study to collect end-of-study data.

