### Sample size

Sample size calculations were carried out using G*Power V.3.1.9.2 software [25]. The sample size was calculated based on data from Tjelle et al. [15], a relatively similar polyphenol-rich berry juice intervention study that observed a reduction in SBP of 6.2 mmHg compared to placebo. Assuming equal standard deviation in both group and by considering pooled value of the standard deviation = 8.8, a significance level of *α* ≤ 0.05 and statistical power of 80%, the minimum sample size will be 66 patients will be required to detect a change of this size in the SBP level. To account for a drop-out rate of approximately 20%, we plan to recruit 80 participants (40 randomized to each group).

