### Compliance

All participants will be called biweekly to assess their compliance. Participants will be asked to mark a reminder note for the daily consumption of the packages. They will be given a sheet of paper that includes the code, the next visit date, two columns entitled “one package daily” and another column entitled “Date” to record their regular consumption of package. Patients are asked to bring empty packages to the hospital at the end of the study period.

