#### Blood pressure

Before and after of 8-week intervention, 24-h ABPM with an automatic monitor in oscillatory mode will be performed in the electrophysiology department of the hospital. The change in blood pressure during the 24-h period is recorded by this device. The blood pressure cuff is placed and fixed around the upper left arm. The digital blood pressure monitoring machine itself is attached to a belt around the waist or hangs on the neck. Technician checks that battery life is sufficient for 24 h and checks if the machine operates well. The cuff inflates every 30 min in the day and every 1 h in night time as per the settings and then slowly deflates to record the blood pressure in its memory. Patients will be asked to have their usual lifestyle and activities at this 24-h ambulatory blood pressure monitoring.

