#### Safety procedures

We will record and report all adverse events. Participants with abnormal research samples will be referred to a specialist.

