#### Statistical analyses

Data analysis will be done using SPSS version-21 software. A per-protocol analysis will be carried out, in which only participants who complete the full study protocol will be included. All results will be assessed for normality, and skewed distributions will be log-transformed before analysis. To describe the quantitative data, the mean and standard deviations will be used, and to describe the qualitative data, frequency and percent will be used. Between-group differences will be tested by independent sample *t* test and Mann-Whitney *U* test as the parametric and nonparametric tests respectively. Paired-sample *t* test and nonparametric Wilcoxon signed ranks test will be used for evaluating within-group differences in normally and non-normally distributed data, respectively. Chi-square or Fisher exact tests will be used for qualitative variables. Parametric or nonparametric analysis of covariance (ANCOVA) will be used for adjusting baseline levels for comparing between groups results. In this study, *P* value less than 0.05 will be considered statistically significant.

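### The drop-out rule does not separate stopping the product from leaving the study, so the plan makes no provision for a week-8 outcome after a side effect or missing telephone responses

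*Protocol article*

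**What the plan says.** All references are to the protocol article.

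- **Eligibility:** "The drop out criteria include any side effects, refusing to continue the study, missing telephone responses, and any restrictive illness". The participant's own right to leave is a separate sentence: "Participants are allowed to withdraw from the study at any time". The list therefore also reaches people who have not asked to leave. No severity, relatedness or number of calls is given.
- **Compliance:** "All participants will be called biweekly to assess their compliance".
- **Setting:** after the product is handed out, "The next meeting will be at the end of the study to collect end-of-study data". No early-termination or off-product visit is described.
- **Blood pressure:** "Before and after of 8-week intervention, 24-h ABPM with an automatic monitor in oscillatory mode will be performed". Systolic pressure is the primary objective.
- **Statistical analyses:** "A per-protocol analysis will be carried out, in which only participants who complete the full study protocol will be included".
- **Safety procedures:** "We will record and report all adverse events".
- **Sample size:** 66 patients are needed, and 80 are recruited to allow for about 20% drop-out.

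**The concern.** Stopping the powder and leaving the study are different events, and the Eligibility section treats them as one. A participant who reports a side effect, or does not respond to the telephone calls, may still be willing to attend at week 8. As written, that person is a drop-out, with no visit foreseen and no place in the analysis.

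The loss is not neutral. Side effects can depend on which powder was taken. The calls exist to check compliance, so missing responses may mark poor adherence. The investigator who assigns the groups is not blinded (Randomization/blinding), and so open a criterion leaves room for judgements that differ by arm. The participants who remain are then selected on events after randomisation, and the protection that randomisation gives to the comparison of systolic pressure is weakened.

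This is a question of data collection as well as of analysis set. Changing the analysis to one by randomised group does not recover a reading that was not taken.

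**Working it through.** **1. The passages side by side.** A criterion can be met at any time after randomisation (Eligibility). The next planned contact in person is the end-of-study visit (Setting), and the only ABPM after baseline belongs to it (Blood pressure). Someone dropped at week 3, for example, has no systolic reading after baseline. If one were obtained, the rule in Statistical analyses would exclude it, because that person has not completed the full protocol.

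**2. The plan's own sample size.** Inputs from Sample size: difference 6.2 mmHg, SD 8.8 mmHg, alpha 0.05, power 80%. Sidedness is not stated; two-sided reproduces the figure.

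- Two-sample t test, non-central t with non-centrality 6.2 / (8.8 × √(2/n)): n = 33 per arm gives 2.86 and power 80.5%. Total 66, as stated.
- 66 × 1.2 = 79.2, rounded to the stated 80.
- A loss of 20% of 80 is 16 participants, leaving 64, or 32 per arm if evenly split.

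**3. Power with and without the lost readings.**

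| Situation | Per arm | Difference (mmHg) | Power |
|---|---|---|---|
| 20% lost and not measured | 32 | 6.2 | 79.2% |
| All 80 measured, no dilution | 40 | 6.2 | 87.5% |
| All 80 measured, 20% stop and have no effect (assumed) | 40 | 6.2 × 0.8 = 4.96 | about 70% |

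The first row is close to the planned 80%. The second is a ceiling, and realistic dilution could more than cancel the gain. Power is therefore no argument for the change.

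**4. Illustration of bias (assumed values, not in the document).** Let a share p of one arm be lost, and let the mean change of those lost be D mmHg worse than that arm's overall mean. Suppose that loss in the other arm is unrelated to outcome. The completer mean of the first arm then moves by p × D / (1 − p).

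| p | D (mmHg) | Shift (mmHg) | Share of 6.2 |
|---|---|---|---|
| 10% | 5 | 0.1 × 5 / 0.9 = 0.56 | 9% |
| 10% | 10 | 0.1 × 10 / 0.9 = 1.11 | 18% |
| 20% | 5 | 0.2 × 5 / 0.8 = 1.25 | 20% |
| 20% | 10 | 0.2 × 10 / 0.8 = 2.50 | 40% |

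**5. Effect on the test.** With no true effect and 32 per arm, the standard error is 8.8 × √(2/32) = 2.2 mmHg.

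- A shift of 1.25 mmHg gives non-centrality 1.25 / 2.2 = 0.57 and two-sided type I error 8.7%.
- A shift of 2.5 mmHg gives 2.5 / 2.2 = 1.14 and 20.1%.

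A larger sample does not remove this shift.

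**The case against.** **The text never says that week-8 measurement is withheld from drop-outs.** This is right. The time table and flow diagram are not visible, and an article condenses the full protocol. A reader might infer that the ABPM is never taken in these people; the document supports only that it is not provided for. The concern stands all the same, because the article states the drop-out rule and the completers-only rule outright. Read together they exclude these participants, whatever detail lies elsewhere.

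**A single missed call need not be enough.** A reader might infer that it is. The wording is plural and sets no number, and with no visit between baseline and the end it could equally describe someone who can no longer be reached. That would be ordinary loss to follow-up, which an invitation may not recover. What stands is that the threshold is undefined.

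**Safety reporting is not confined to completers.** Also right. The commitment to record and report adverse events has no such limit, and a side effect that triggers drop-out is known at that moment. A reader might infer that tolerability cannot be judged, but the text does not support that. At most, observation of later events is shortened.

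**Part of the loss cannot be avoided.** The expected 20% also covers refusal and restrictive illness, and nothing says what share comes from side effects or missing telephone responses. The change would recover some of the 16, not all.

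**New readings would be discarded anyway.** Under the present Statistical analyses section they would be. This is a reason to change both sections together, not to leave the rule as it is.

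**Conclusion.** The concern holds as a badly fixed rule. Following the text as written loses primary-outcome data, or excludes it, for reasons that arise after randomisation and may depend on product or adherence. The direction and size of any bias cannot be known from the document. The range of 1.25 to 2.5 mmHg, with type I error of about 9% to 20%, rests on three assumptions: a 20% loss in one arm, a 5 to 10 mmHg worse mean change in those lost, and outcome-unrelated loss in the other arm. It shows what is possible and is not an estimate for this trial.

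The sample size is correct on its inputs, and the case does not rest on power. The change should be made because it removes an avoidable source of selection at low cost.

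**What to change.** Leave decisions on taking the product to clinical judgement; the list of criteria need not be edited for this purpose. Make two linked changes.

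1. **Eligibility and Setting.** State that meeting a drop-out criterion does not by itself end study follow-up. Every randomised participant is invited to the planned week-8 ABPM, blood and urine visit, on or off product, unless consent is withdrawn. The reason and date of stopping are recorded by arm.
2. **Statistical analyses.** Analyse all these readings by randomised group, and keep the per-protocol analysis as a sensitivity analysis.

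Neither change is sufficient alone: the first collects readings that the present analysis rule would discard, and the second cannot use readings that were not taken.

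**Cost.** The week-8 visit is already planned for all 80, so the practical burden is a few more ABPM slots than completers alone would use. Recruitment had begun on 20 January 2020 (Trial status), so this is an amendment that must be agreed, recorded with its justification (Protocol amendments) and communicated to participants (Trial status). The estimated effect will be somewhat diluted by people who stopped the powder, as the 4.96 mmHg example shows. That is the price of a comparison that randomisation protects.
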